**Results:**

Recruitment to the trial started in July 2020. The study was initiated with 17 primary care physicians. We expect the inclusion period to last for approximately 6 months. We expect to complete data collection by the end of 2021 and plan to disseminate the results subsequently.

**Conclusions:**

The HOROSCOPE (Home Telemonitoring of Arterial Hypertension With Antihypertensive Treatment Titration: Randomized Controlled Prospective Trial) study will provide important new evidence that could shed some light on the feasibility and impact of telemonitoring and self-monitoring in a Tunisian population of patients with hypertension who consult primary care physicians.

**Trial Registration:**

ClinicalTrials.gov NCT04607239; https://clinicaltrials.gov/ct2/show/NCT04607239

**International Registered Report Identifier (IRRID):**

DERR1-10.2196/26184

## Introduction

### Background

Hypertension is one of the main risk factors for cardiovascular disease and the leading cause for global morbidity and mortality [1,2]. Despite the availability of effective treatment, the control of hypertension remains insufficient [3]. It has been suggested that self-monitoring in the management of hypertension is an effective method of improving blood pressure control [4,5]. Nevertheless, isolated self-monitoring has not been associated with better blood pressure control; it would be more beneficial if it was used in combination with other interventions, such as integrating primary care physicians in a telemonitoring approach. Despite conflicting evidence, a Scottish study involving general practitioners reported a significant reduction in blood pressure over a period of 6 months [6]. Furthermore, telemonitoring could help physicians with antihypertensive treatment titration [7], as shown in another trial (TASMINH2 [Telemonitoring and/or Self-monitoring of Blood Pressure in Hypertension 2]), which demonstrated that the telemonitoring with home titration group had lower blood pressure than that of the usual care (control) group after 12 months [8]. Moreover, a recent study (TASMINH4 [Telemonitoring and/or Self-monitoring of Blood Pressure in Hypertension 4]) aimed to determine whether telemonitoring resulted in a lower blood pressure by comparing it to usual care (control) and self-monitoring only [9]. The trial was a parallel randomized controlled trial that was conducted with 142 general practitioners in the United Kingdom and included patients who were hypertensive, aged over 35 years, had a blood pressure of >140/90 mm Hg, and were willing to self-monitor their blood pressure. A total of 1182 patients were randomly assigned to blood pressure self-monitoring (self-monitoring group: n=395), blood pressure self-monitoring with telemonitoring (telemonitoring group: n=393), or usual care (control group: n=394). After 12 months, patients’ systolic blood pressure (SBP) was lower in both the self-monitoring and telemonitoring groups compared to that of the usual care group (mean 137, SD 16.7 mm Hg and mean 136, SD 16.1 mm Hg vs mean 140.4, SD 16.5 mm Hg, respectively). No statistically significant differences between the self-monitoring and telemonitoring groups were recorded. This study showed that self-monitoring, with or without telemonitoring, can be used to guide the titration of antihypertensive medicines in primary care. The observed drops in blood pressure in this study indicated an approximate 20% and 10% reduction in the risk of stroke and coronary heart disease, respectively [9]. The results of this study deserve to be confirmed, especially since this study’s approach can be economically interesting [10] in the context of a resource-limited country with failing health economics. It would be of great use to evaluate this approach with general practitioners in Tunisia—a country in which the prevalence of hypertension in urban areas is significantly greater than that in rural areas (*P*<.001) and only 38.1% of patients with hypertension are aware of their hypertension [11].

### Research Questions

The aim of the HOROSCOPE (Home Telemonitoring of Arterial Hypertension With Antihypertensive Treatment Titration: Randomized Controlled Prospective Trial) study is to demonstrate the impact of telemonitoring on blood pressure control among patients with hypertension.

The trial will address the following three main research questions: (1) does telemonitoring improve treatment compliance and blood pressure control in newly diagnosed or poorly controlled patients with hypertension, (2) does telemonitoring improve patients’ quality of life, and (3) does telemonitoring reduce the incidence of cardiovascular complications?

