### Sample Size

A sample size of 199 subjects per group is required for 80% power, assuming a mean difference in the reduction of SBP of at least 5 mm Hg between the two study groups and an SD of 15 mm Hg. Considering a patient dropout ratio of 15%, the study will need to recruit 230 subjects in each group.

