### Baseline and Follow-up Clinic Examinations

Patients will undergo an initial baseline clinic examination, during which clinical measurements, demographic data, and past medical histories will be collected and electrocardiogram exams and biological examinations will be conducted.

A validated blood pressure monitor (ROSSMAX X3; Rossmax Swiss GmbH) will be used for blood pressure measurements. After 1 month, a satisfaction questionnaire—the Medical Outcomes Study Short Form-12 questionnaire [12]—will be completed by participants, so that we can assess their quality of life.

Twenty-four–hour ambulatory blood pressure monitoring (ABPM) will be performed for all included patients to analyze their blood pressure profiles through the use of a Holter monitor (Contec ABPM 50; Contec Medical Systems). Ambulatory blood pressure measurements will be scheduled to acquire a blood pressure reading every 30 minutes from 6 AM to 10 PM and every 60 minutes from 10 PM to 6 AM. The cuff will be placed on participants’ nondominant arms. Of the 48 possible measurements, at least 32 (67%) must be available. Otherwise, ABPM will be repeated. The Holter monitor must not get wet (eg, via a swimming pool, bath, or shower), and usual activities must be maintained. After installing the Holter monitor, study participants can return to their usual activities. They will be invited to return to the clinic 24 hours later, so that we can collect the data from their monitors. The results will be interpreted by a cardiologist.

Randomization will take place 1 month after participants’ inclusion, that is, after the collection of at least 32 interpretable ABPM measurements. All patients will be asked to attend 2 follow-up clinics within 6 months. The clinical follow-up data to be collected are detailed in Table 1.

**Table 1 table1:** Timetable for patient data collection throughout the trial.

Collected data	Baseline (inclusion visit)	After 29 days (1 day prior to the randomization visit)	After 3 months (follow-up visit 1)	After 6 months (follow-up visit 2)
Sociodemographics	✓			
Past medical history	✓			
Clinical examination^a^	✓	✓	✓	✓
Biological tests^b^	✓		✓	✓
ECG^c^	✓	✓		✓
SF-12^d^		✓		✓
ABPM^e^		✓		✓
Treatment compliance		✓	✓	✓
Side effects		✓	✓	✓

^a^The clinical examination will mainly include the assessment of blood pressure (systolic and diastolic blood pressure), BMI, and heart failure New York Heart Association stage.

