### Statistical Analysis

Categorical variables will be expressed as frequencies and percentages, while continuous variables will be expressed as means with SDs. An analysis of variance will be performed to compare the two study groups in terms of the primary end point. The normality of continuous data will be assessed with the Shapiro-Wilk test. Furthermore, we will use a general linear model for repeated measures to compare the marginal means of Gaussian quantitative dependent variables before and after the intervention (a Bonferroni test will be considered). A nonparametric test (the Friedman test) will be used for the comparison of non-Gaussian quantitative variables before and after intervention. The Cochran Q test will be performed to compare binary dependent variables before and after intervention. Subgroup analyses will be performed by age (<65 years and ≥65 years), sex, and the severity of hypertension. Differences between continuous variables will be evaluated with a 2-tailed Student *t* test or by its correction, as appropriate. The differences among the categorical variables will be evaluated with the Pearson chi-square test. All tests will be considered significant at the cutoff value of *P*<.05.

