#### Secondary Outcomes

The following will be our secondary outcomes:

The percentage of patients who exhibit a change of 5 mm Hg in average 24-hour diastolic blood pressure from baseline to the 6-month follow-upThe percentage of patients who exhibit a change of 10 mm Hg and 5 mm Hg in average 24-hour blood pressure from baseline to the 6-month follow-upThe change in blood pressure load (Textbox 2) percentages from baseline to the 6-month follow-upThe change in dipping (Textbox 2) percentages from baseline to the 6-month follow-upThe percentage of patients taking more than 80% (400/500) of the antihypertensive medications at the 6-month follow-upThe percentage of patients with changes in mean 12-Item Short Form Survey scores from baseline to the 6-month follow-upClinical outcomes, including hospitalization rates and emergency room admissions related to high blood pressure, adverse effects, or other reasons

Blood pressure load and dipping definitions.

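### Research question 2 asks whether quality of life improves, but the only SF-12 outcome is a percentage of patients with changes, without direction or size

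*Protocol article*

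**What the plan says.** Research Questions lists, as the second of three main questions, "does telemonitoring improve patients’ quality of life". Baseline and Follow-up Clinic Examinations says that the SF-12 "will be completed by participants, so that we can assess their quality of life". Table 1 schedules it on day 29, one day before the randomisation visit, and again at month 6.

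Secondary Outcomes contains one SF-12 item: the percentage of patients with changes in mean SF-12 scores from baseline to month 6. No direction, minimum change or SF-12 score is named, and there is no other quality-of-life outcome. The blood pressure outcomes beside it at least carry a cut-off, for example "The percentage of patients who exhibit a change of 5 mm Hg in average 24-hour diastolic blood pressure".

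Statistical Analysis gives general rules by type of variable. For categorical variables: "The differences among the categorical variables will be evaluated with the Pearson chi-square test". For continuous variables: "Differences between continuous variables will be evaluated with a 2-tailed Student" *t* test or its correction. It also names a repeated-measures general linear model for Gaussian quantitative variables and the Friedman test for non-Gaussian ones. The SF-12 is not mentioned there.

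**The concern.** The question is directional and the outcome is not. A patient whose score falls is a patient with a change, just as one whose score rises is. With no minimum size, any movement on a many-valued score qualifies, so the count would be close to everybody in each arm and could hardly differ between arms.

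The wording is also not coherent. A percentage of patients needs a yes/no status for each patient, whereas a mean score belongs to a group. A reader cannot tell whether a responder count or a comparison of means is specified, and the two fall under different tests in Statistical Analysis.

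At stake is the answer to one of three declared main questions. Either the published outcome is analysed as a count and says almost nothing, or it is replaced by a comparison of means that the article did not state. A choice made after the data are seen would be open to the charge of selection.

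**Working it through.** **The article's own figure.** There is no sample-size or power statement for the SF-12. The only one concerns systolic pressure: "A sample size of 199 subjects per group is required for 80% power". Its inputs are a between-group difference of 5 mm Hg and a standard deviation of 15 mm Hg. The two-sided 5% formula gives n = 2 × [15 × (1.960 + 0.842) / 5]² = 141.3, so 142 per group, not 199. That mismatch is a separate matter. Here 199 serves only as the number evaluable per arm (the 230 to be recruited, less 15%, gives about 195, which changes little).

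**Inputs**
- From the article: 199 per arm, 1:1 allocation, two-sided 0.05.
- Assumed, because the article gives no SF-12 figures: change SD 6 to 11 points, true benefit 2 or 3 points, mean change 0 in control, and normally distributed changes.
- c is the largest movement still counted as no change: 0.05 for scores kept to one decimal, 0.5 for whole points, 1 as a generous allowance.

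**Step 1: percentage changed.** With mean change m,

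P(changed) = 1 − Φ((c − m)/SD) + Φ((−c − m)/SD).

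Example with SD 9 and c = 0.5:
- control, m = 0: 2 × [1 − Φ(0.0556)] = 95.6%
- telemonitoring, m = 3: 1 − Φ(−0.278) + Φ(−0.389) = 1 − 0.3906 + 0.3487 = 95.8%

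**Step 2: power of the comparison of percentages.** With p̄ = 0.957, the standard error is √(0.957 × 0.043 × 2/199) = 0.0204. The difference of 0.0024 is 0.12 standard errors, and Φ(0.12 − 1.96) ≈ 3%. This is the chance of a significant result favouring telemonitoring. Counting false results in the other direction brings it to about 5%.

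**Step 3: power of the comparison of means, same patients.** SE = 9 × √(2/199) = 0.902. Then 3/0.902 = 3.325, and Φ(3.325 − 1.960) = 91%.

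For a 3-point benefit:

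| SD | Changed, control vs telemonitoring (c = 0.05) | c = 0.5 | c = 1 | Power, percentages | Power, means |
|---|---|---|---|---|---|
| 6 | 99.3% vs 99.4% | 93.4% vs 94.1% | 86.8% vs 88.3% | 3–7% | 99.9% |
| 9 | 99.6% vs 99.6% | 95.6% vs 95.8% | 91.2% vs 91.6% | 3–4% | 91% |
| 11 | 99.6% vs 99.7% | 96.4% vs 96.5% | 92.8% vs 93.0% | about 3% | 78% |

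For a 2-point benefit the percentages have 3–4% power. The comparison of means has 91% at SD 6, 60% at SD 9 and 44% at SD 11.

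**Step 4: direction.** The Step 1 formula gives the same value for m = +3 and m = −3. An undirected cut-off does not cure this: at SD 8 and a cut of 3 points, a 3-point benefit and a 3-point harm both give 72.7% changed, against 70.8% with no effect.

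**The case against.** The strongest reply is that the phrase about changes in mean scores is a garbled mean-change outcome. On that view nobody would count every small movement, and the general methods for quantitative variables in Statistical Analysis would cover the SF-12. This is a plausible reading of the intent, and it limits the point. A reader might infer that nearly every patient will certainly be counted, but that follows from one literal reading plus SDs from outside the article. What remains is that the text says a percentage of patients, which as a categorical variable goes to the chi-square test, and nothing assigns the SF-12 elsewhere.

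A second reply is that cut-offs, component scores and covariates belong in a statistical analysis plan that is not shown. Their absence alone would indeed be no finding. But the article states an outcome, and that outcome does not match the stated question. A plan that analysed mean scores would be replacing it rather than filling in detail.

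Third, the blood pressure responder outcomes, including the one under Primary Outcome, also name no direction. That is true, and it points to a drafting habit. They do carry a cut-off, however, and the SF-12 item has neither.

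Finally, the equality of benefit and harm holds exactly only for symmetric changes and no drift in control. With drift the two percentages would differ, though only slightly.

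**Conclusion.** The point holds as a defect in how the outcome is defined. The sole SF-12 outcome does not answer research question 2 as worded: it has no direction or minimum size, and it mixes a patient-level percentage with a group mean. On the binary reading, about 87% to 100% of patients in both arms would count as changed, and a 2- to 3-point benefit would be detected about 3% to 7% of the time. A comparison of means on the same patients has 78% to 99.9% power for 3 points and 44% to 91% for 2 points. All of these rest on the assumed SDs of 6 to 11 points, the assumed benefits and no control-arm change.

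A reader might go further and infer that the trial cannot answer the quality-of-life question. The article does not support that: the SF-12 is scheduled for all patients before randomisation and at month 6, so the data would allow an answer. The outcome is secondary, but it is the only support for a declared main question, so it should be corrected.

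**What to change.** Restate the outcome as the between-arm difference in mean SF-12 score at month 6, for each SF-12 score to be reported. Estimate it from a linear model adjusted for the day-29 pre-randomisation score and investigation centre (the stratification factor), and give the difference with its 95% CI. Say in Statistical Analysis that this is the SF-12 analysis. An unadjusted or repeated-measures comparison of means would also address the question; adjusting for the day-29 score generally gives a more precise estimate.

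If a percentage is kept, make it supportive and define it in advance as improvement of at least a stated and justified number of points.

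The cost is rewording one secondary outcome and adding one line of analysis. No new data, visits or patients are needed. The change should be documented before SF-12 results are compared by arm.

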## Methods

### Study Design

Our trial will be a multicentric, rater-blinded, prospective randomized controlled trial. The allocation ratio between the intervention and control group will be 1:1. Randomization will be done via the use of an interactive web responsive system, and patients will be stratified by investigation center. Neither participants nor investigators will be masked to the group assignments. However, the cardiologist, who will interpret the results of the primary outcome, will be blinded.

The study is expected to last for an overall duration of 12 months (from the first patient who is enrolled to the last patient who completes the trial). The recruitment period will last for 6 months, and the follow-up interval will be 6 months.

### Participants

Patients with hypertension will be recruited from consultations with primary care general practitioners in the central region of Tunisia. The inclusion and exclusion criteria are outlined in Textbox 1.

Inclusion and exclusion criteria for the HOROSCOPE (Home Telemonitoring of Arterial Hypertension With Antihypertensive Treatment Titration: Randomized Controlled Prospective Trial) study.
**Inclusion criteria**
Aged ≥35 years oldNewly diagnosed hypertensionPoorly controlled hypertensionOne single blood pressure value outside the expected range will not be taken as a definitive indicator of clinical deteriorationBlood pressure should be >140/90 mm Hg at screening for at least 2 visits to allow the inclusion of a patient
**Exclusion criteria**
Orthostatic hypotensionChronic renal failure (serum creatinine level: >200 µmol/L)Acute coronary syndrome, coronary revascularization, or stroke within the past 3 monthsKnown secondary causes of hypertensionPregnancyNew York Heart Association Class III or IV heart failure or left ventricular ejection fraction of <30%Dementia or any other cause that could prevent the implementation of remote monitoring (telemonitoring)

### Recruitment, Screening, and Informed Consent Procedures

Participants will be recruited directly from primary health care centers by general practitioners. Participants will be included during their visit to the outpatient clinic after the verification of their eligibility criteria. When patients meet the eligibility criteria, the investigator will provide them with a study information sheet. Patients showing interest in taking part in the study will be included.

Material compensation will not be offered for participating in the study. Potential participants will be informed about the scientific benefits of their participation and will not be offered any other incentives. In order to obtain informed consent, the investigator will inform the participants about the possible benefits and potential side effects of participating in this study as well as the study duration. Patients will also be informed that their participation will be strictly voluntary and that they can withdraw from the study at any time without stating any reason. They will also be informed that withdrawing from the study will not affect subsequent medical assistance and treatment. Participants will be advised that their personal data will be used by other authorized health care professionals other than their treating physicians as part of the clinical trial. They will be given sufficient time to reflect extensively on their participation decision. The informed consent form will be signed and dated by the investigator following the signature of the participant. The consent form will be retained as part of the study records. A signed copy will be provided to each study participant. Overall patient flow throughout the study is depicted in Figure 1.

**Figure 1 figure1:**
[figure not shown]
Participant flow throughout the study. ABPM: ambulatory blood pressure monitoring; BP: blood pressure; CRA: clinical research associate; SF-12: 12-Item Short Form Survey.

### Sample Size

A sample size of 199 subjects per group is required for 80% power, assuming a mean difference in the reduction of SBP of at least 5 mm Hg between the two study groups and an SD of 15 mm Hg. Considering a patient dropout ratio of 15%, the study will need to recruit 230 subjects in each group.

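### The 199 per group stated for 80% power does not follow from a 5 mm Hg difference and SD 15 mm Hg: as worded these need 142 to 143, and 199 gives about 91% power

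*Protocol article*

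**What the plan says.** The Sample Size section of the protocol article has two sentences. The first gives the evaluable number: "A sample size of 199 subjects per group is required for 80% power". Its inputs are a 5 mm Hg advantage in how far systolic pressure falls, with variability entered as "an SD of 15 mm Hg". The second sentence gives the recruitment target: "Considering a patient dropout ratio of 15%, the study will need to recruit 230 subjects in each group".

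That section gives no significance level or sidedness, and mentions no correlation between visits, design effect or multiplicity adjustment. It does not say whether the SD belongs to the reduction or to a single reading.

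The missing test settings can be taken from elsewhere in the article. Statistical Analysis has "All tests will be considered significant at the cutoff value of *P*<.05" as the significance rule and, for the form of the test, "Differences between continuous variables will be evaluated with a 2-tailed Student *t* test or by its correction, as appropriate". Study Design has "The allocation ratio between the intervention and control group will be 1:1".

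**The concern.** Effect, SD, power and sample size are given together, and the sample size is presented as what the other three require. A reader should be able to reproduce it, and on the plain wording the result is far from 199. The gap of about 40% is too large for rounding or for the difference between a normal and a t calculation.

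What is at stake is knowing how the trial was designed. If 15 mm Hg is the SD of the reduction, the trial is sized for about 91% power on the means. If a larger SD or another inflation lies behind 199, the design power is about 80%, and slightly less after the stated dropout. The article does not let a reader tell which.

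**Working it through.** **Inputs.** Difference 5 mm Hg, SD 15 mm Hg, power 80%, stated n 199, dropout 15% and recruitment 230 per group (Sample Size). Two-sided alpha 0.05 (Statistical Analysis). Allocation 1:1 (Study Design). Statistical Analysis names an analysis of variance for the primary end point. With two groups this is equivalent to the two-sided t test, so the calculation is the same.

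**Attempt to reproduce 199.** n per group = 2 (z₀.₉₇₅ + z₀.₈₀)² (SD/difference)² = 2 × (1.960 + 0.842)² × (15/5)² = 141.3, so 142. The exact noncentral t calculation gives 143. The stated 199 is 199/142 = 1.40 times this.

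**Power at the stated n.** Power ≈ Φ[(5/15) × √(n/2) − 1.960].
- n = 199: Φ(3.325 − 1.960) = 91.4% (91.3% by exact t).
- n = 195: Φ(3.291 − 1.960) = 90.8% (90.7% by exact t).

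**Other settings with 5 mm Hg and SD 15.**

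| Setting | n per group |
|---|---|
| One-sided 0.05, 80% power | 112 |
| Two-sided 0.025, 80% power | 172 |
| Two-sided 0.05, 90% power | 190 |
| Two-sided 0.01, 80% power | 211 |

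None of these gives 199.

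**What would give 199 at 80% power and two-sided 0.05**, changing one input at a time:
- SD of the reduction: (5/2.802) × √(199/2) = 17.8 mm Hg.
- Difference: 15 × 2.802 × √(2/199) = 4.2 mm Hg.
- Design effect: 199/142 = 1.40.
- A Bonferroni split over four tests comes close, at 201.

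**If 15 mm Hg is the SD of a single reading.** The SD of the reduction is then 15 × √[2(1 − ρ)], where ρ is the correlation between baseline and 6 months. The article gives no ρ, so the values below are assumptions that show the range.

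| ρ (assumed) | SD of reduction | n per group for 80% power |
|---|---|---|
| 0 | 21.2 | 283 |
| 0.3 | 17.75 | 198 (199 by t) |
| 0.5 | 15.0 | 142 |

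**Dropout step.** Inflating 199 for 15% loss gives 199/0.85 = 234.1, so 235. The stated 230 leaves 230 × 0.85 = 195.5, about 195 evaluable. Multiplying instead gives 199 × 1.15 = 228.9, close to 230, which suggests how the figure arose but does not prove it. The cost is small:
- SD of the reduction 15: power falls from 91.4% to 90.8%.
- SD of the reduction 17.8: Φ[(5/17.8) × √(199/2) − 1.960] = 80.0% falls to Φ[(5/17.8) × √(195/2) − 1.960] = 79.2%.

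Starting from 142 to 143 evaluable, the same inflation would give 168 to 169 recruited per group.

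**Which outcome the calculation covers.** It concerns a difference in means, which matches the primary outcome in the Abstract (Methods). Outcomes, Primary Outcome instead defines the percentage of patients with a 10 mm Hg change. Suppose reductions are normal with SD 15, the arms differ by 5 mm Hg and the mean reduction in the control arm is 0 to 10 mm Hg (an assumption). Comparing those percentages then needs 223 to 245 per group without continuity correction, and 195 per group gives about 71% to 75% power. The responder definition therefore does not explain 199 either.

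**The case against.** The strongest defence is that the paragraph never says what the SD refers to. With 15 mm Hg at each visit and a correlation of 0.3, the t calculation returns 199 at 80% power. An article may leave such details to the full protocol. This part stands: a reader might infer that the stated power, SD and sample size cannot all be right, and the article does not support that. All three can hold if one further input was used and not reported. For the same reason it would be too strong to say that 199 arises only at an SD of 17.8, since a smaller difference or a design effect would also produce it.

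The defence does not remove the point. The sentence attaches the SD to the difference in reduction, and the 0.3 is found by working backwards from 199. The article prints the inputs and says that they require 199, which goes beyond leaving out a detail.

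It is also fair to say that the consequence is limited. On the plain reading the comparison of means has more power than claimed. The dropout slip is about 2% of the recruitment target (235 against 230). Recruitment began in July 2020 and data collection was expected to finish by the end of 2021, so the target itself may no longer be open to change. These arguments bear on severity, and I accept them there.

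**Conclusion.** The point holds as a failure to reproduce. With SD 15 mm Hg as the SD of the reduction, two-sided alpha 0.05 and 1:1 allocation, the stated inputs need 142 to 143 per group, and 199 gives about 91% power. Getting 199 at 80% takes an input that the article does not contain. The dropout step is a side note worth less than one point of power.

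A reader might go further and conclude that the trial is underpowered. The plain reading shows the opposite for the comparison of means: about 91% at 195 evaluable. Power near 79% follows only from an SD of the reduction near 17.8, which the article does not state. Nor does the 91% carry over to the 10 mm Hg responder percentage.

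This should be fixed as a matter of traceability. It does not threaten the validity of the comparison.

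**What to change.** Rewrite the Sample Size paragraph so that it reproduces:
- Say what the SD of 15 mm Hg refers to, state two-sided alpha 0.05, and report any correlation, design effect or other inflation actually used.
- If 15 mm Hg is the SD of the reduction, state that 142 to 143 evaluable per group give 80% power, and that 230 recruited (about 195 evaluable after 15% dropout) give about 91% for the comparison of mean 24-hour systolic change.
- If another SD, correlation or inflation was used, report it with the power at 195 evaluable. Do not adopt a correlation, such as 0.3, because it happens to return 199.
- Keep 230 per group and declare about 195 evaluable in place of 199.
- State that this power applies to the difference in means given in the Abstract, not to the responder percentage under Outcomes, Primary Outcome.

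The cost is one paragraph of text. No extra patients are needed.
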